### Participant timeline {13}

A schema of this trial and a timeline is presented in the SPIRIT figure below (see Table 1). The total study duration will be the length of PICU admission plus 12 months follow-up. Patients receive the intervention during the first 48 h after enrolment.

**Table Tab1:**
[figure not shown]
Table 1

### Sample size {14}

The primary outcome is the cumulative respiratory morbidity score 12 months after PICU discharge. A classical sample size based on a independent sample *t* test between two groups was calculated, assuming a 20% difference in cumulative mean respiratory morbidity score. This resulted in a required sample size of 148 patients (*N* = 74 intervention versus *N* = 74 placebo) to demonstrate a 20% reduction in respiratory symptoms in the intervention group compared to the placebo with an alpha of 5% and power of 80%. Considering a potential maximum drop-out of 20% per group because of withdrawal of consent or loss to follow-up, we need to enrol *N* = 89 patients per group. Thus, the total sample size is 178 patients.

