## Background and rationale {6a}

Paediatric acute respiratory distress syndrome (PARDS) is a manifestation of severe, life-threatening lung injury. The prevalence of PARDS in critically ill, mechanically ventilated children may be as high as 10% of all children admitted to the paediatric intensive care unit (PICU) with mortality rates ranging up to 40–50% [1]. The disease is characterised by massive pulmonary inflammation, alterations in surfactant homeostasis and ventilation/perfusion mismatching leading to severe hypoxemia and multiple organ dysfunction [2]. Mechanical ventilation (MV) has added significantly to the survival of PARDS patients but also induces a pulmonary inflammation (biotrauma) that aggravates pre-existing lung injury (double-hit), a concept known as ventilator-induced lung injury (VILI) [3–5].

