## Statistical methods

### Statistical methods for primary and secondary outcomes {20a}

Data is analysed with an intention-to-treat approach. The primary outcome measure is a continuous outcome parameter. First, it will be tested for normality using the Shapiro-Wilk test. Dependent upon the outcome of this test, in the univariate analysis, the primary outcome will be displayed as mean ± standard deviation or median (25–75 interquartile range) and analysed using either the Student *t* test or the Mann-Whitney *U* test. Paired analysis will be used to compare the primary outcome with its baseline value. In multivariate analysis, zero inflated regression analysis is used to adjust for possible confounding by age, gestational age, family history of asthma and/or allergy, season in which questionnaire was filled out, parental smoking, and parental perception of the outcome of randomisation. Depending on the outcome of the analysis on randomisation outcome, variables that were significantly different between the intervention and control arm will also be adjusted for in the multivariate analysis. On top of that, we will adjust if there is an imbalance in the use of (non-) pulmonary specific ancillary treatment used during PICU admission.

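### Enrolling 89 per group does not keep 74 evaluable at the stated 20% maximum drop-out (93 are needed), and the allowance leaves out deaths

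*Protocol article*

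**What the plan says.** All the figures are in Sample size {14} of the protocol article. The calculation is a two-group t test, "assuming a 20% difference in cumulative mean respiratory morbidity score", "with an alpha of 5% and power of 80" per cent. "This resulted in a required sample size of 148 patients", split equally as 74 and 74. The allowance follows: "Considering a potential maximum drop-out of 20% per group because of withdrawal of consent or loss to follow-up", which takes each group to 89. "Thus, the total sample size is 178 patients".

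The outcome is a parental questionnaire completed 12 months after PICU discharge (Plans for assessment and collection of outcomes {18a}).

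On mortality the article says two things. Background and rationale {6a} describes the disease "with mortality rates ranging up to 40–50" per cent. The Discussion calls the rates fairly low but very variable, and uses this to explain why mortality was not made the primary outcome. No rate is assumed for the trial itself.

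**The concern.** Two things look wrong with the step from 74 to 89.

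- A drop-out rate applies to the children enrolled, so the evaluable number must be divided by one minus the rate. Adding 20% to the evaluable number gives too few.
- The allowance names only two causes of loss. Death before 12 months is a third, and it removes the primary outcome just as surely.

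At stake is whether 178 children support the 80% power that readers will hold the result against. The more losses exceed what 178 covers, the less a null result says about a true 20% reduction.

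**Working it through.** **Inputs from Sample size {14}:** 74 evaluable per group, 1:1 allocation, alpha 5%, power 80%, drop-out 20% per group, 89 enrolled per group. **Assumption:** a two-sided test, since sidedness is not stated.

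**1. Reproducing the plan's figure.** 74 × (1 + 0.20) = 88.8, rounded up to 89; 2 × 89 = 178. The printed figures come out this way.

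**2. The inflation that keeps 74.** 74 / (1 − 0.20) = 92.5, rounded up to 93; 2 × 93 = 186. The shortfall is 4 per group, 8 in total.

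**3. What 89 per group covers.** 1 − 74/89 = 15/89 = 16.9%.

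**4. Power at the stated maximum drop-out.** The article prints no mean or SD, so the standardised effect was solved from the plan's own 74 per group, 80% power and 5% two-sided alpha. The t test gives d = 0.4636. At 20% drop-out, 89 × 0.8 = 71.2 remain per group. Power with d = 0.4636 is 78.4%, or 78.3% with a whole 71.

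Sidedness hardly matters. With a one-sided test, the normal approximation gives d = 0.4088 for 74 per group. At 71.2 per group, √(71.2/2) × 0.4088 − 1.645 = 0.794, which is a power of about 78.6%.

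**5. Adding deaths.** Let m be the proportion who die before the 12-month questionnaire, with 20% drop-out among survivors. The values of m are assumptions. Evaluable per group = 89 × (1 − m) × 0.8; enrolment needed per group = 74 / ((1 − m) × 0.8), rounded up. The same d is used throughout.

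| Assumed deaths | Total attrition | Evaluable per group | Power | Needed per group |
|---|---|---|---|---|
| 0% | 20% | 71.2 | 78.4% | 93 |
| 5% | 24% | 67.6 | 76% | 98 |
| 10% | 28% | 64.1 | 74% | 103 |
| 20% | 36% | 57.0 | 69% | 116 |
| 40% | 52% | 42.7 | 56% | 155 |

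**6. The same point from the other side.** With 89 enrolled per group, the survivor drop-out that still leaves 74 is 1 − 74 / (89 × (1 − m)). With 5% deaths this is 1 − 74/84.55 = 12.5%; with 10% deaths, 1 − 74/80.1 = 7.6%. Once deaths reach 16.9%, no room is left for any other loss.

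**The case against.** **The slip is small.** The plan calls 20% a maximum. If total attrition stays at or below 16.9%, 74 per group remain and power is at least 80%. At the full 20% the cost is 1.6 percentage points. This stands. A reader might infer that 80% power is not delivered; the article does not support that as an unconditional statement.

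**Mortality of 40–50% should not be read into this trial.** This also stands. The figure is the top of a range, the Discussion describes the rates as fairly low, and Eligibility criteria {10} excludes several high-risk groups, including children after bone marrow transplantation and those with treatment limitations. The rows with deaths show sensitivity and are not a forecast. What remains is that the allowance does not mention deaths at all.

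**Loss to follow-up might be meant to include deaths.** If so, 20% is the total and only the arithmetic needs correcting. The text does not say this, and one sentence would settle it.

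**A stronger reading about the spread is tempting.** The implied SD is 0.2/0.4636 = 0.43 of the mean. For a non-negative score this allows at most 0.43²/(1 + 0.43²), about 16%, of children to score zero. Statistical methods {20a} says that "zero inflated regression analysis is used to adjust for possible confounding by age" and other factors, so a reader might infer that the assumed SD is too small and true power far lower. The documents do not establish this. They give no mean, SD or expected share of zeros, the full protocol may state the SD, and planning such a model does not show that more than 16% will score zero. Any power figure on this ground would rest on invented inputs.

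**Conclusion.** The point holds in a limited form. The enrolment figure is wrong on the article's own numbers: 20% drop-out from 74 evaluable per group requires 93 per group (186), and 178 covers 16.9%. At the stated maximum, power is 78.4% instead of 80%. Steps 1 to 3 need no outside assumption; the power figure assumes a two-sided test and the standardised effect implied by 74 per group.

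The omission of deaths is also on the face of the text. Its size is open because no trial mortality is given. Across assumed deaths of 5 to 40%, on top of 20% drop-out among survivors, evaluable numbers run from about 68 to 43 per group and power from about 76% to 56%. A material loss of power therefore depends on mortality; the arithmetic slip alone does not produce it.

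**What to change.** In Sample size {14}, do one of two things:

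- state 93 per group, 186 in total, for 20% attrition; or
- keep 178 and state that it covers total attrition of 16.9%, with about 78% power at 20%.

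In either case, name death before the 12-month questionnaire as a cause of attrition, say whether the 20% includes it, and give power over a range of mortality, as in the table above.

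Cost: the first option adds 8 children, or more if deaths are allowed for on top of the 20%. The second adds none and changes only the text, with a stated power that is slightly less favourable.

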### Recruitment {15}

All potential subjects will be informed about the study as soon as possible, even prior to meeting the criteria due to the limited time for enrolment when criteria are met.

## Assignment of interventions: allocation

### Sequence generation {16a}

Patients will be randomised to rocuronium bromide or isotonic saline by the ServiceDesk Clinical Research Office (SD-CRO, UMCG). They will create a randomisation list for the whole study, ahead of time, using blocked randomisation with a block size of 4.

### Concealment mechanism {16b}

The A15 Pharmacy of the UMC Groningen, coordinated by the Department of Clinical Pharmacy and Pharmacology of the UMC Groningen, will prepare and label the study medication. The rocuronium bromide will be refilled under good manufacturing practice (GMP) conditions into a new 10 mL vials to match placebo, that will be adequately labelled for the study. The NaCl 0.9% will be put in a vial matching the rocuronium vial and will also be adequately labelled for the study.

The rocuronium bromide as well as the NaCl 0.9% will be packaged in non-transparent boxes per 10 vials. This way, one box of vials will contain sufficient study medication for one patient for 48 h. The non-transparent boxes will ensure blinding of the study team in case of slight colour differences between rocuronium bromide and the NaCl 0.9%.

### Implementation {16c}

The study team enrols the participant and always uses the first blinded kit (lowest number) available and hereby assigns them (blinded) to the study arm and the interventions of the study.

## Assignment of interventions: Blinding

### Who will be blinded {17a}

Full blinding of the clinical team cannot be ensured because children randomised to the control arm may display spontaneous movements and/or breathing. For this reason, the study team will be prohibited from participating by any means in the clinical care of the participant. On top of that, the statistical analysis and long-term outcome assessment staff are blinded to the study arm, and aggregate outcome data will be restricted to an unblinded statistician and the data safety monitoring board.

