### Trial design {8}

The Paediatric ARDS Neuromuscular blockade (PAN) trial is a phase IV, multicentre, randomised, double-blind, placebo-controlled superiority trial.

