### Strategies to improve adherence to interventions {11c}

Most of the interventions take place during admission on the PICU by research staff. The respiratory morbidity score questionnaires will be administered electronically by email and reminders will be sent automatically after 1 week.

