### Procedure for unblinding if needed {17b}

The randomisation schedule is provided by the ServiceDesk Clinical Research Office and kept by the Department of Clinical Pharmacy and Pharmacology of the UMC Groningen to ensure blinding until the end of the study. In case of a medical emergency, the pharmacist on call can be consulted for unblinding.

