## Data collection and management and storage of biological specimens

### Plans for assessment and collection of outcomes {18a}

#### Primary outcome

The respiratory morbidity will be assessed using a structured questionnaire in agreement with recommendations from the American Thoracic Society [29]. This parental questionnaire studies the presence of respiratory symptoms including cough, wheezing and shortness of breath during rest and/or activity. The questionnaire consists of 14 items that can only be answered by yes or no. The questionnaire is commonly used and validity of the items in the respiratory morbidity score has been shown [29, 30]. Upon discharge, parents or legal caretakers are asked for their e-mail address and phone number; the personalised link to the web-based questionnaire will be e-mailed to them 12 months after PICU discharge. If there is no response within 7 days, they will receive a reminder via e-mail. The questionnaire is personalised and anonymised. The same questionnaire is used upon PICU admission to study baseline respiratory morbidity.

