### Confidentiality {27}

Identifying information will be removed and substituted by an unique study number. Nonetheless, a randomisation list will be remained with the name linked to the study number. The randomisation list will be securely stored by the local investigator and is only available for the study team and on request for the monitor, data safety monitoring board and the pharmacy. After the trial, the data will be stored secured at the secured long storage of the UMCG until it is deemed appropriate to be destroyed.

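### The blinding described does not assure that the parents, who score the primary outcome, are unaware of the arm, and the planned adjustment for their perception is a weak remedy

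*Protocol article*

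**What the plan says.** Trial design {8} states that the study "is a phase IV, multicentre, randomised, double-blind, placebo-controlled superiority trial", and the Methods paragraph of the abstract uses the same label.

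Who will be blinded {17a} qualifies it: "Full blinding of the clinical team cannot be ensured because children randomised to the control arm may display spontaneous movements and/or breathing". That section gives two main safeguards. The study team is kept out of clinical care, and "the statistical analysis and long-term outcome assessment staff are blinded to the study arm". Parents are not mentioned.

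The Primary outcome text under {18a} describes 14 items answered yes or no: "This parental questionnaire studies the presence of respiratory symptoms including cough, wheezing and shortness of breath during rest and/or activity". Parents receive a personal web link 12 months after PICU discharge. No staff rating is described.

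Statistical methods {20a} adds parents' perception of the allocation to the covariates of the multivariate model. The primary outcome definition, in the abstract and in Outcomes {12}, has no such covariate.

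**The concern.** The safeguard that {17a} offers for outcome assessment is the blinding of staff, but staff do not produce the primary score. Parents do, and the items are symptoms they must notice, remember and judge. A parent who believes the child was or was not paralysed may answer differently for that reason alone.

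If such beliefs follow the true arm and change the answers, the comparison of arms mixes treatment effect with reporting. A result presented as double-blind with blinded assessment would then claim more protection than the design gives.

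**Working it through.** **1. Who is masked, and who scores.**

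| Role | Masking according to the article | Scores the primary outcome? |
|---|---|---|
| Clinical team | Cannot be ensured ({17a}) | No |
| Study team | Kept out of clinical care ({17a}) | No |
| Long-term outcome staff | Blinded ({17a}) | No; the questionnaire is parental ({18a}) |
| Analysts | Blinded ({17a}) | No |
| Parents | Not stated | Yes |

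The one role that scores the endpoint is the one whose masking is not described. That parents see the child move or breathe is an inference, but the cue named in {17a} is open to anyone at the bedside.

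**2. The adjustment in {20a}.** Including perception as a covariate shows that the authors expect parents to form a view. It is a weak remedy for three reasons.
- If the view comes from seeing movement, it is a proxy for the arm, and adjusting for it can take out part of a real effect.
- If the view comes from how the child fared, it is a consequence of the course of illness, and adjusting for it can add bias.
- It enters only the multivariate model, not the t test or Mann-Whitney comparison.

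The covariate lists also disagree. The abstract and Outcomes {12} include day-care and omit perception; {20a} includes perception and omits day-care. Whether the adjustment belongs to the primary result is therefore not settled.

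**3. Illustration of size.** The documents give no rate of unblinding and no estimate of reporting bias, so the shift below is assumed.

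Inputs from Sample size {14}: 74 evaluable per arm, alpha 5%, power 80%, target difference 20% of the mean score. Sidedness is not stated; two-sided is assumed. No mean or SD is given, so the 74 cannot be reproduced forward. Solving backwards with a t test:
- standardised effect d = 0.464 (normal approximation: (1.960 + 0.842) × √(2/74) = 0.461);
- implied SD/mean = 0.20 / 0.464 ≈ 0.43.

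With no true effect and a net reporting shift equal to a fraction f of the target, the test statistic is centred at

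s = f × 0.464 / √(2/74) = f × 2.82,

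and the two-sided rejection probability is Φ(s − 1.96) + Φ(−s − 1.96).

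| Net shift, % of mean | f | s | Type I error |
|---|---|---|---|
| 0 | 0 | 0 | 5.0% |
| 2 | 0.10 | 0.28 | 5.9% |
| 5 | 0.25 | 0.71 | 10.9% |
| 10 | 0.50 | 1.41 | 29.2% |
| 15 | 0.75 | 2.12 | 56.2% |

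As a guide to what a net shift means: if half of parents infer the arm correctly and move their answers by 5% in opposite directions by arm, the net shift is 0.5 × (5% + 5%) = 5%. If they move by 10%, it is 0.5 × (10% + 10%) = 10%. These too are assumptions. The table ignores any effect of the perception adjustment.

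**The case against.** The strongest reply is that the authors saw the problem and dealt with it. They disclose the limit of the blind in {17a} and adjust for parental perception in {20a}, which requires that perception be recorded. Vials are matched, boxes are opaque, kits are numbered and analysts are blinded. The score is taken a year after discharge, control children only may move, and {22} notes that patients with severe lung injury are often deeply sedated. The direction of any parental expectation is also unknown, since the article itself reports conflicting adult evidence and possible harms. All of this stands and lowers the likely bias. It does not extend masking to the parents, and the adjustment has the weaknesses shown above.

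Some stronger readings are tempting but not supported.
- *The study team can see allocations.* Confidentiality {27} says "The randomisation list will be securely stored by the local investigator and is only available for the study team", whereas under {17b} the schedule is "kept by the Department of Clinical Pharmacy and Pharmacology of the UMC Groningen to ensure blinding until the end of the study". But {27} describes its list as linking name to study number and mentions no treatment arm, and {18a} refers to a subject identification code list. The list in {27} is most naturally that key under the wrong name.
- *Research staff deliver care despite the bar in {17a}.* The sentence "Most of the interventions take place during admission on the PICU by research staff" is loose, but reading ventilator values for the case report form is data collection, and those staff do not score the primary outcome.
- *There is no objective outcome to set beside the score.* Lung clearance index and functional residual capacity are secondary outcomes at 12 months, measured by technicians in equipped centres.
- *The blind gives the primary result no protection.* The measures listed above rule that out.

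**Conclusion.** The point holds in a limited form: the blind as described does not assure masking of the person who scores the primary outcome, so an unqualified double-blind label overstates the design. The plan acknowledges the risk, but through a post-randomisation covariate that its own primary outcome definition omits.

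The size of any bias is unknown. On the assumptions stated (two-sided 5%, 74 per arm, SD/mean about 0.43 as implied by the sample size, no true effect), a net shift of a quarter of the target difference roughly doubles the type I error to about 11%, and a shift of half the target raises it to about 29%. This shows that modest reporting bias would matter; it is not evidence that such bias will occur. The list in {27} is a wording correction only.

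**What to change.** 1. In the abstract, {8} and {17a}, describe the design as placebo-controlled with matched study drug and blinded analysts, with the bedside team and parents possibly unblinded.
2. Record the parents' guess of the arm and their reason for it at PICU discharge, before any follow-up score, and report guesses by arm as a blinding check. The article does not say when perception is recorded; if the full protocol already fixes this, only the timing and the report by arm need confirming.
3. Instruct the clinical team not to tell parents which arm they suspect.
4. Reconcile the covariates in the abstract and {12} with those in {20a}, and make the perception-adjusted model a sensitivity analysis.
5. In {27}, rename the list as a subject identification log without allocation, consistent with {17b} and {18a}.

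The cost is a less favourable design label, one extra question at discharge and some wording. Because enrolment has begun, the discharge guess can be collected only for children discharged after the change.

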### Procedure for unblinding if needed {17b}

The randomisation schedule is provided by the ServiceDesk Clinical Research Office and kept by the Department of Clinical Pharmacy and Pharmacology of the UMC Groningen to ensure blinding until the end of the study. In case of a medical emergency, the pharmacist on call can be consulted for unblinding.

## Data collection and management and storage of biological specimens

### Plans for assessment and collection of outcomes {18a}

#### Primary outcome

The respiratory morbidity will be assessed using a structured questionnaire in agreement with recommendations from the American Thoracic Society [29]. This parental questionnaire studies the presence of respiratory symptoms including cough, wheezing and shortness of breath during rest and/or activity. The questionnaire consists of 14 items that can only be answered by yes or no. The questionnaire is commonly used and validity of the items in the respiratory morbidity score has been shown [29, 30]. Upon discharge, parents or legal caretakers are asked for their e-mail address and phone number; the personalised link to the web-based questionnaire will be e-mailed to them 12 months after PICU discharge. If there is no response within 7 days, they will receive a reminder via e-mail. The questionnaire is personalised and anonymised. The same questionnaire is used upon PICU admission to study baseline respiratory morbidity.

